# Effectiveness of diabetes self-management education via a smartphone application in insulin treated type 2 diabetes patients – design of a randomised controlled trial (‘TRIGGER study’)

**DOI:** 10.1186/s12902-018-0304-9

**Published:** 2018-10-22

**Keywords:** Type 2 diabetes mellitus, Insulin therapy, mHealth, eHealth, Self-management, Behavioural change, Triggers, Cost-effectiveness, Diabetes education, Hypoglycaemia

## Abstract

**Background:**

Health care providers aim to stimulate self-management in type 2 diabetes (T2DM) patients. However, they have a limited number of patient contacts to do this. With the growing number of T2DM patients, innovative and cost-effective interventions to promote self-management are needed. We aim to evaluate the effectiveness of diabetes self-management education via a smartphone app in T2DM patients on insulin therapy.

**Methods:**

Non-blinded two-arm multi-centre randomised controlled superiority trial with parallel-groups and equal randomisation (‘TRIGGER study’). Eligible patients are 40–70 years, on insulin therapy since at least 3 months, with HbA1c > 53 mmol/mol (> 7%). In total 228 patients will be recruited. The intervention group (*n* = 114) will receive diabetes self-management education via a smartphone app to trigger diabetes self-management: unidirectional text messages, free of charge, evidence and psychological theory based, with regard to dietary habits, physical activity, hypoglycaemia and glucose variability. Patients choose their preferred frequency (two to six times per week), topics (two or three additionally to hypoglycaemia, which is an obligatory topic), and duration (6 or 9 months). The control group (*n* = 114) will receive care-as-usual. The primary study endpoint is the HbA1c level after a follow-up of 6 months. The percentage of patients who achieve an HbA1c level ≤ 53 mmol/mol (≤7%) without hypoglycaemia (plasma glucose < 3.5 mmol/L (< 63 mg/dL)) is a co-primary outcome. Secondary outcomes are body mass index, waist circumference, insulin dose, lipid profile, blood pressure, number of hypoglycaemic events, glycaemic variability, self-management (SDSCA), food habits (FFQ), physical activity (IPAQ), health status (EQ-5D-5 L, SF36), diabetes-dependent quality of life (ADDQoL), diabetes treatment satisfaction (DTSQ), satisfaction with the app, the cost-effectiveness of the intervention after 3 months, and sustainability of the intervention effect (3 months extra follow-up in intervention group to compare prolonged to discontinued use of the app). We will use the intention-to-treat principle to analyse data.

**Discussion:**

Innovative solutions are needed to improve the (cost-) effectiveness of self-management for the increasing number of T2DM patients. This trial will provide evidence on the effectiveness of a newly developed smartphone app, designed to trigger diabetes self-management.

**Trial registration:**

Dutch Trial Register NTR5515, registration date: 18 November 2015 (prospectively registered).

**Electronic supplementary material:**

The online version of this article (10.1186/s12902-018-0304-9) contains supplementary material, which is available to authorized users.

## Background

Self-management forms a crucial part of type 2 diabetes (T2DM) treatment, especially for insulin treated individuals. It includes healthy food choices, frequent exercising, regular blood glucose monitoring, and dietary and insulin dose adjustments related to physical activity. These adaptations are necessary to achieve optimal glycaemic control (without much variability and hypoglycaemia) and weight loss, and to prevent both microvascular and macrovascular complications. However, for most patients, diabetes self-management is challenging and difficult to maintain. Besides, results of self-management interventions are often effective in the short-term, but have mixed long-term results [1]. Health care providers aim to stimulate self-management, but due to the limited number of diabetes monitoring visits they are in the position to trigger diabetes self-management only a few times a year [2]. Moreover, with the growing number of T2DM patients and the expected shortage of health care providers in some countries, innovative and (cost-) effective solutions to promote self-management are needed.

A potential low-cost intervention to stimulate diabetes self-management may be the use of a smartphone app. The number of diabetes apps has tremendously increased during the past years. In the iTunes store alone, there was a ten-fold increase from 60 in 2009 [3], to 622 in 2013 [4]. When the number of diabetes apps from Google Play, BlackBerry, Windows and Ovi Store are added to that number, the total number of diabetes apps already exceeded 1800 in 2013 [4]. Unfortunately, many of these diabetes apps have not been studied in medical research, i.e. they are not evidence based. In one study, only 16 out of the 87 identified apps could be found in medical literature; 71 apps were solely found in the iTunes Store [5].

A common feature of a diabetes app is self-monitoring of blood glucose levels, blood pressure, physical activity, weight, medication intake and food intake [3, 5–7]. For blood glucose, blood pressure and physical activity (step counter), automatic data entry is often possible, but apps facilitating these features are likely to be associated with higher costs. Another common feature is interactive communication with health care providers [3, 7]. Many of the apps that have been investigated showed to be effective [6–8]: HbA1c decreased [7, 9, 10] and self-management improved [11]. However, for most patients, daily entry of personal data is a tedious task [6], often resulting in infrequent or non-use of the app [11]. Besides, technologies for automatic data transfer are more expensive, as is true for interactive communication and tailored feedback from health care providers [12].

Another type of a smartphone app, that may have a more sustainable effect on self-management, is an educational app that sends automated app-messages that function as behavioural triggers; it requires less effort from both health care providers and patients, and may be a low-cost solution compared to the abovementioned strategies. We hypothesise that receiving cost free behavioural triggers on preferential topics and with a self-chosen frequency, sent as app-messages via a smartphone app, will result in better diabetes self-management and improved glycaemic control, less weight gain and less glucose variability with less hypoglycaemic events in T2DM patients on insulin therapy.

### Theoretical framework of the intervention

Behavioural triggers (also known as prompts, stimuli or cues to action) play a pivotal role in behaviour change [13]. They play an important role in the ‘Health Belief Model’ [14], in Leventhal’s self-regulation model [15] and in the ‘Transtheoretical Model of Behaviour Change’ [16]. In the ‘Fogg Behavior Model’, triggers are even of paramount importance [13]. In all these theories, behavioural triggers have some overlapping characteristics. Firstly, a trigger stimulates the individual to engage in health-promoting behaviour [14, 15]. Secondly, a trigger can be either internal (i.e. signs and symptoms such as pain or dyspnoea) or external, emerging in various forms: from a warning label on a product to a reminder e-mail from the dentist [14, 15]. Finally, external triggers can have a motivational element (e.g. a trigger that highlights fear), can increase the individuals’ ability to behaviour change, or can function as a signal (e.g. a reminder) [13]. While triggers are import for behavioural change, for a given behaviour to occur more than a single trigger is needed, namely a certain level of perceived health threat, severity, self-efficacy and a sufficient level of motivation [13–16]. The intensity of the trigger will depend on the presence and level of for example motivation (i.e. the less motivated, the more intense the trigger should be to achieve the intended behaviour) [13, 14]. On the other hand, receiving a behavioural trigger can be the last factor to overcome barriers and to adapt the intended behaviour.

Behavioural triggers can be sent as text messages. Evidence on the effectiveness of unidirectional triggers delivered by mobile phone technology (either via app or SMS) so far is mainly based on studies with a small number of patients and a short duration, focussing on feasibility [8, 17–19]. Moreover, studies were conducted in patient samples that may not be representative for Western countries, e.g. in Iraqi patients and in resource-poor patients in the United States (for a greater part low income groups and from ethnic minority groups, frequently without health insurance) [20, 21]. Furthermore, the sustainability of app-triggers or SMS-triggers on diabetes self-management is unknown, but important for successful implementation.

## Methods

### Research questions

We aim to determine the effectiveness of unidirectional evidence based app-messages on self-management of insulin treated T2DM patients. This will be determined via the following research questions (1) What are the effect of the intervention on HbA1c level and on the percentage of patients who achieve an HbA1c level ≤ 53 mmol/mol (≤7%) without hypoglycaemia (plasma glucose < 3.5 mmol/L (< 63 mg/dL) after a follow-up period of 6 months? (2) What are the effects of the intervention on body mass index (BMI), lipid profile, blood pressure, waist circumference, prescribed insulin dose, number of hypoglycaemic events and glucose variability after a follow-up period of 6 months? (3) What are the effects of the intervention on self-management activities, food habits, physical activity, health status, diabetes related quality of life and diabetes treatment satisfaction after a follow-up of 6 months? (4) What is the cost-effectiveness of the app-trigger intervention compared to usual care? and (5) Is the intervention effect sustainable after 3 months of prolonged versus discontinued use of the app in the intervention group?

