### Outcomes

The primary study outcome is glycaemic control, defined as the HbA1c level after a follow-up of 6 months in the app-trigger group compared to the control group. As a co-primary outcome we will analyse the percentage of patients who achieve an HbA1c level ≤ 53 mmol/mol (≤7%) without any hypoglycaemic event (plasma glucose < 3.5 mmol/L (< 63 mg/dL)). Secondary outcomes are BMI, body weight, waist circumference, insulin dose, lipid profile, blood pressure, number of hypoglycaemic events, glycaemic variability, self-management, food habits, physical activity, health status, diabetes-dependent quality of life, diabetes treatment satisfaction and satisfaction with the app (intervention group only) after 6 months. Moreover, we will investigate the cost-effectiveness of the intervention after 6 months, and the sustainability of the intervention effect. The latter is investigated in the intervention group only: we will compare the effect of 3 months prolonged use of the app to stopping with the use of the app, on HbA1c, on the percentage of patients who achieve an HbA1c level ≤ 53 mmol/mol (≤7%) without any hypoglycaemic event, BMI, and health status. Prolonged users are individuals from the intervention group who choose to continue the intervention after 6 months (T6); discontinued users are those who do not continue using the app after T6.

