### Measurements

At baseline patients will complete seven questionnaires, regarding self-management activities, food habits, physical activity, health status, quality of life, diabetes dependent quality of life and diabetes treatment satisfaction. For a detailed description of the questionnaires see Table 2. Patients are asked to complete the baseline questionnaires before randomisation. After 3 months (T3) patients will complete two questionnaires; after 6 months (T6) patients will complete eight (control group) to nine (intervention group: extra questionnaire on satisfaction with the app) questionnaires (see Table 2). Patients in the intervention group also complete one questionnaire after 9 months of follow-up (T9) (see Table 2). All clinical variables are obtained by an online case report form (eCRF) completed by the practice nurse or diabetes nurse at T0, T6 and for the intervention group also at T9. In addition to anthropometric (length, weight, waist circumference and blood pressure) and laboratory parameters (HbA1c and lipid profile), the following demographic and clinical variables are collected: age, duration of diabetes, ethnicity, level of education, smoking status (current, former, never), presence of microvascular complications (nephropathy, retinopathy, neuropathy) and macrovascular complications (cardiovascular diseases), and diabetes medication use (including insulin injection frequency and dose).

**Table 2 Tab2:** Description of questionnaires

Questionnaire	Description	Score range	Completed at
Summary of Diabetes Self-Care Activities Measure (SDSCA) [34]	11 Items assessing several aspects of the diabetes regimen: diet, exercise, blood glucose testing, foot care and smoking. Items measure how many days a patient has performed self-care activities in the last 7 days.	10 Items rated on an 8-point Likert scale, measuring how many days an activity is performed in the last week. One item measures smoking status (yes/no) and the amount of cigarettes smoked in the last week. Each of the domains is measured separately.	T0, T6
Food habits questionnaire (FFQ) [35]	18 Items assessing patient’s habits with regard to preparation of food, fatty food intake, dietary products and fruit and vegetable intake.	All items differ in the scoring ranges, varying from four scoring options (never, sometimes, frequently or always) to eight options (never to 7 days a week)	T0, T6

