Diabetes Treatment Satisfaction Questionnaire (DTSQ) [41]	Includes 8 items. In question 1 and 4–8 the satisfaction with the treatment is better if the scores are higher. In questions 2 and 3, lower scores indicate blood glucose levels closer to the ideal, and higher scores indicate problems.	Scores range per item from 6 (very satisfied) to 0 (very dissatisfied); total score range 36 to 0.	T0, T6
Satisfaction and usability of the app	Questionnaire newly developed by the researchers contains questions about the satisfaction with regard to receiving app-triggers, frequency, timing and comprehensibility, see Additional file 1.	All items will be rated on a 5-point Likert scale.	T6^a^
Outpatient clinic visits and paramedical health care use	Newly developed questionnaire contains one question on outpatient clinic visits (for patients recruited from primary care) or GP visits (for patients recruited from hospitals) and three questions on paramedical health care use: whether patients have visited a dietician, a physiotherapist or a specialised feet therapist the past 3 months.	All four questions are answered with yes or no. In case of a ‘yes’, patients have to fill in how many times they have visited the physician/therapist.	T3, T6

Abbreviations: *T0* baseline measurement, *T3* measurement after 3 months of follow-up, *T6* measurement after 6 months of follow-up, *T9* measurement after 9 months of follow-up

^a^Completed by intervention group only

For the cost-effectiveness analysis, data on health care use are extracted from both the electronic medical record and from the questionnaires sent to the participants at T3 and T6. The number of hypoglycaemic events and the glycaemic variability are extracted at T6 (control group and intervention group) and at T9 (intervention group) from patient diaries, handed out to the patients at the start of the study. These diaries are designed for the purpose of this study only: patients record information on all hypoglycaemic events during the study, and once a week blood glucose values throughout the day (fasting plasma glucose and three pre-prandial values). For an overview of the study design and procedures: see Fig. 3.

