## Discussion

Self-management is crucial for T2DM patients, especially for those on insulin therapy. However, to be effective, self-management education should be intensive [32], and thus will be costly. Moreover, worldwide there is a rapid increase in the number of T2DM patients. Against that background, cost-effective solutions to promote diabetes self-management are pivotal. If our newly developed app proves to be cost-effective, it could be used by all insulin treated T2DM patients because the messages are evidence-based and not region-specific. The topics ‘dietary habits’ and ‘physical activity’ can also be used to stimulate diabetes self-management in the non-insulin users. The app may be a standalone intervention but can also be used as part of a more comprehensive program. A possible limitation for delivery at scale might be the attitude of health care providers towards new technologies. Whereas the use of automated unidirectional messages may seem simple, a recently conducted systematic review and meta-analysis on this topic showed that one-way and two-way messages had a very similar effect, while two-way messages are usually more resource intensive [33].

An operational issue that may occur during the study is that patients stop reading the text messages, while they are not formally withdrawn from the study. However, since we are able to monitor the number of reminder SMSs sent (SMS fall back), we will be able to monitor the ‘adherence’. Moreover, this study is a real-life pragmatic trial; in real-life we also expect non-use or infrequent use of a smartphone app. Another issue that may arise, is that because all patients are informed about the study before they sign informed consent and before they are randomised, patients in the control group may also get aware of the existence of diabetes apps. Some patients in the control group might start using other diabetes apps during the study. To overcome this, patients in the control group will not have access to the smartphone app developed for the purpose of this trial, but will be offered to use it immediately after. Besides, both patients in the intervention and control group are equally able to use other diabetes apps.

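### Research question 5 asks whether the intervention effect is sustained, but at nine months there is no randomised or usual-care comparator, only self-selected continuers and stoppers

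*Protocol article*

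**What the plan says.** The Research questions section puts the fifth question as: "Is the intervention effect sustainable after 3 months of prolonged versus discontinued use of the app in the intervention group". The Outcomes section defines the primary outcome as HbA1c at six months in the app group against the control group. It then describes sustainability: "The latter is investigated in the intervention group only: we will compare the effect of 3 months prolonged use of the app to stopping". The outcomes for this part are HbA1c, the composite of HbA1c target without hypoglycaemia, BMI and health status.

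Membership of the two groups is the patient's decision: "Prolonged users are individuals from the intervention group who choose to continue the intervention after 6 months (T6"), while "discontinued users are those who do not continue using the app after T6".

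The Measurements section sets who is measured when. Clinical variables are recorded "at T0, T6 and for the intervention group also at T9". Diary data are taken "at T6 (control group and intervention group) and at T9 (intervention group"). Table 2 marks the nine-month EQ-5D-5L as an intervention-group questionnaire.

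On access for controls, the section on the intervention says that they may use the app once the study is over. The Discussion says that they do not have it during the trial "but will be offered to use it immediately after". Neither gives a month.

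**The concern.** Whether an effect is sustained is a question about a difference between app and usual care at a later time. That difference is randomised and measurable at T6. At T9 the usual-care side is not measured, so the quantity named in question 5 is not available there, and no analysis can recover data that were not collected.

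The Background says that the lasting effect of such messages is unknown and matters for implementation, and that self-management programmes tend to work in the short term with mixed later results. The T9 follow-up is the part of the trial aimed at this gap. If prolonged and discontinued users look alike at T9, the report could read as evidence that the benefit lasts after stopping, when the data would fit a benefit that has gone in everyone.

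**Working it through.** **1. What the T9 contrast identifies.** Let E be the app effect versus usual care at T9, and U the mean HbA1c that a group would have had under usual care. Subscripts c and s stand for continuers and stoppers.

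- Planned contrast at T9 = (E_c − E_s) + (U_c − U_s).
- The second term is selection. Continuing is chosen at T6, so motivation and response up to T6 can differ between the groups.
- Even with the second term at zero, the first gives only the difference between the two effects, not the level of either.

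The planned effect in the Sample size section is 0.41 percentage points. Taking it as a reduction and assuming no selection:

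| E_c | E_s | Contrast | Meaning |
|---|---|---|---|
| −0.41 | −0.41 | 0 | fully kept in both |
| 0 | 0 | 0 | lost in both |
| −0.41 | −0.205 | −0.205 | kept in continuers, halved in stoppers |
| −0.205 | 0 | −0.205 | halved in continuers, lost in stoppers |

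Rows 1 and 2 cannot be told apart, nor can rows 3 and 4. Randomising continuation would remove the selection term but leave this ambiguity.

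**2. Change from T6.** The change within one group is the change in E plus the change in U. Without controls at T9, the change in U is unknown. Subtracting the two groups' changes cancels any movement in U that they share, but again leaves only a difference between changes in effect.

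**3. The plan's own figure.** Inputs from the Sample size section: difference 0.41, SD 1.1, power 80%, and 5% read as a two-sided significance level.

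- Normal approximation: n per arm = 2 × (1.960 + 0.842)² × 1.1² / 0.41² ≈ 113, or 226 in total.
- Two-sample t-test: 113.96, so 114 per arm and 228 in total. This matches the protocol.

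**4. Precision at T9 (illustration).** Assumptions: all 114 intervention patients reach T9, SD stays 1.1 and there is no confounding. The document gives no split, so a range is shown. Half-width = 1.96 × 1.1 × √(1/a + 1/b). Power is for a difference of 0.41 by two-sided t-test at 5%.

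| Larger / smaller group | 95% half-width | Power |
|---|---|---|
| 57 / 57 | 0.40 | 50% |
| 68 / 46 | 0.41 | 49% |
| 80 / 34 | 0.44 | 44% |
| 91 / 23 | 0.50 | 35% |
| 103 / 11 | 0.68 | 21% |

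For the arms as randomised, 114 versus 114, the half-width is 1.96 × 1.1 × √(2/114) = 0.29. If only half of the controls (57, an assumption) had a routine value near nine months, it would be 1.96 × 1.1 × √(1/114 + 1/57) = 0.35.

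**The case against.** The strongest reply is that the protocol is open and consistent. It names its comparator, discontinued users, in the question itself, defines both groups under Outcomes, and says that this part concerns the intervention arm only. On that reading, question 5 is a limited secondary aim with its own contrast, and the dispute is partly about the word effect. This stands in part: there is no hidden error or internal contradiction, and a reader who inferred that question 5 has no comparator at all would be wrong. What is missing is a randomised or usual-care comparator.

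Diverging courses after T6, with stoppers drifting back and continuers holding, would also be informative. That is fair, but the evidence would be observational and would still not place either group against usual care.

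Two further inferences are tempting and unsupported. One is that controls receive the app straight after their T6 visit. T6 is their last measurement, but the text ties access only to the end of the study. The other is that seasonal or treatment drift between T6 and T9 would distort the planned comparison by some share of 0.41. Drift common to both groups cancels in that comparison, and the document gives no drift figure, so no such size is claimed.

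Finally, a comparison of arms at T9 pools continuers and stoppers, so it does not answer whether prolonging helps. That is correct. It answers whether the effect of having been offered the app is sustained.

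**Conclusion.** The point holds as a design weakness in a secondary question. With T9 data from the intervention arm only, the effect versus usual care cannot be estimated at nine months, and the prolonged-versus-discontinued contrast cannot show that it was kept or lost. This rests on the stated measurement schedule and needs no numerical assumption.

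The precision figures are illustrative and depend on the assumed split, full retention and SD 1.1. They show that, even without confounding, the within-arm contrast has at most about 50% power for a difference the size of the planned effect. The six-month randomised comparisons stand as planned.

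**What to change.** Extract the control patients' HbA1c and weight nearest to nine months from the medical record, which already feeds the case report form. State that the app is offered to controls only after T9. Name intervention versus control at T9, as randomised, as the test of sustainability, and report prolonged versus discontinued use as descriptive.

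The costs are one further extraction for up to 114 controls and possibly a three-month delay in an app offer that serves as a recruitment incentive. With two to four usual-care visits a year, some controls will have no value near nine months, and T9 ascertainment will be less uniform in controls than in the intervention arm. The extraction covers HbA1c and BMI only. The hypoglycaemia composite and health status would need diaries and a questionnaire from controls as well.

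If this is not feasible, restate question 5 as an exploratory, non-randomised description of the course from T6 to T9 among continuing and stopping app users, and draw no conclusion that the intervention effect is sustained. That costs only a wording change.
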